**Relevance for the patient:**

The potential benefit for the patient consists in shortened meconium passage, improved feeding tolerance, shorter time of parenteral nutrition and intravenous access and therefore lower sepsis morbidity and shorted hospital stay.

**Adverse events and withdrawal**:

Severe adverse events leading to withdrawal from the study:

Ileus

Volvolus

NEC

death

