Visceral osteopathy: Proponents of [visceral](http://en.wikipedia.org/wiki/Visceral) osteopathy state that the visceral systems (the internal organs: digestive tract, respiratory system, etc.) rely on the interconnection [synchronicity](http://en.wikipedia.org/wiki/Synchronicity) between the motion of all the organs and structures of the body, and that at optimal health this harmonious relationship remains stable despite the body's endless varieties of motion. The idea is that both *somato-visceral* and *viscero-somatic* connections exist, and manipulation of the somatic system can affect the visceral system (and vice-versa).Practitioners contend that visceral osteopathy relieves imbalances and restrictions in the interconnections between the motion of all the organs and structures of the body—namely, nerves, blood vessels, and fascial compartments. During the 1940s, osteopaths like H V Hoover and M D Young built on the work of Andrew Taylor Still to create this method of assessment and manipulation. The efficacy and basis of this treatment remains controversial even within the osteopathic profession.

Especially in children these techniques are well accepted because they are likely to cause no pain or other negative side effects. However, no evidence based data concerning safety and efficacy of osteopathic treatment in infants- especially in premature infants- are available so far.

Therefore, in the present study visceral osteopathic techniques are applied with the aim to accelerate meconium evacuation and establish proper gastrointestinal function in VLBW-infants . Furthermore the safety and efficacy of the applied osteopathic techniques should be surveyed.

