The time to complete meconium evacuation is defined as day of life on which the last meconium was passed. Documentation of stool consistency, colour and amount will be continued until the end of the infants’ stay at the NICU. The observation period ends when the infant was transferred or discharged.

Data collection:

The following data will be recorded:

Before the first osteopathic treatment:

· Gestational age

· Birth weight

· Birth length

· Head circumference at birth

· APGAR

· Umbilical cord-PH

· Clinical condition of the abdomen (size, tension, peristaltic,

apparent standing intestinal loops)

· Stooling pattern

· Ventilation and ventilator support (PEEP)

For the whole duration of the study period, following data was recorded daily:

· Body weight

· Amount of parenteral fluids in ml/kg

· Enteral nutrition supply in ml/kg (Human milk or formula)

· Fortification of human milk

· Gastric residuals

· Stooling pattern

· Clinical condition of the abdomen (size, tension, peristaltic, apparent standing intestinal loops)

· Ventilation and ventilator support (PEEP and flow)

· Feeding intolerance

· Enemas

· Glycerin suppositories

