**Primary outcome:**

time to complete Meconium evacuation in days.

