**Secondary outcome:**

introduction of enteral feeding in days, feeding volume on day 14th

time to full enteral feeding in days,

**Statistical analysis** :

Given the non-normal distribution of the data, all comparisons will be performed using non-parametric tests. The Mann-Whitney U test will be used to detect treatment effects between the groups. Kaplan-Meier curves will be plotted to visualize differences in the time to complete meconium evacuation between the groups. Comparison of the curves will be performed using the log rank test. Multiple Cox regression models will be used to identify the possible influence of the covariates birth weight and GA. For all tests, a p-value < 0.05 was considered to indicate statistical significance. SPSS statistical software system (SPSS Inc., Chicago, IL, version 10.0) will be used for all calculations.

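### Withdrawal from the study for ileus, volvulus, NEC or death conflicts with stool charting to the end of the NICU stay and, if it ends follow-up, can bias the primary comparison

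*Protocol*

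**What the plan says.** Protocol, Adverse events and withdrawal, consists of one line and a list. The line reads "Severe adverse events leading to withdrawal from the study"; the list is ileus, volvulus, NEC and death. It speaks of the study and not only of study treatment.

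Protocol, Design, sets the outcome and the follow-up. "The time to complete meconium evacuation is defined as day of life on which the last meconium was passed", and the primary outcome is "time to complete Meconium evacuation in days". Stool consistency, colour and amount are charted for as long as the infant is in the NICU, and "The observation period ends when the infant was transferred or discharged". No exception is made for infants withdrawn because of an adverse event.

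Protocol, Statistical analysis, tests the effect as follows: "The Mann-Whitney U test will be used to detect treatment effects between the groups". It adds "Kaplan-Meier curves will be plotted to visualize differences in the time to complete meconium evacuation between the groups" and "Comparison of the curves will be performed using the log rank test". It does not say how a withdrawn infant or a death enters these analyses.

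The introduction closes with a safety aim: "Furthermore the safety and efficacy of the applied osteopathic techniques should be surveyed". The listed primary and secondary outcomes cover only meconium passage and feeding.

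**The concern.** The four events happen after randomisation. Three are bowel failures that bear directly on when the last meconium is passed, and the fourth ends observation. The intervention is manual mobilisation of the gut, mesentery and colon, so the treatment itself could plausibly cause some of these events. The protocol states that no evidence-based safety data exist for osteopathy in premature infants.

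A rule that takes infants out of the study for such events can therefore select on a consequence of the treatment. If one arm loses more of its slow infants, the rest of that arm looks faster than it is. The same events are the natural material for the safety aim, yet they appear only as reasons to leave, with no planned comparison by arm.

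**Working it through.** **1. The two rules side by side.** Under Design, an infant with NEC who stays in the NICU is charted until transfer or discharge. Under Adverse events and withdrawal, that infant has left the study. The protocol does not say which rule governs. If charting continues and the data are used, little is lost. If withdrawal ends data collection, the primary outcome is missing for that infant unless evacuation was already complete.

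**2. What the planned methods do if withdrawal ends follow-up.**
- Mann-Whitney needs one value or rank per infant. A withdrawn infant is omitted, or the last stool seen before withdrawal is entered as the last meconium, which turns a possible failure into an early completion.
- Kaplan-Meier and log-rank censor at withdrawal. For ileus, volvulus or NEC the reason for censoring is linked to the time still to come, so the censoring is informative.

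**3. Inputs for the size.**
- Total 40 (Protocol, Sample size). Blocks of 4 suggest 1:1, so 40/2 = 20 per arm (assumed).
- Significance level 0.05, sidedness not stated. Taken as two-sided, the nominal rate of falsely favouring osteopathy is 0.05/2 = 2.5%.
- Event rates: not given, so assumed and varied.
- Spread of evacuation times: not given, so the 40 cannot be reproduced. Read as a 20% relative difference in means with 80% power, two-sided, 40 implies SD/mean = 0.20 × √(20/2) / (1.960 + 0.842) = 0.632/2.802 ≈ 0.226. This value was used to generate times. It hardly matters here: with no true effect, a rank test depends only on the order of the infants.

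**4. Adverse case: no true effect, the slowest infants exit and are omitted, Mann-Whitney.**

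| Removed, osteopathy vs control | Shift in difference of medians (% of mean time) | Falsely favours osteopathy |
|---|---|---|
| 0 vs 0 | 0 | 2.3 to 2.5% |
| 2 vs 0 | −2.7% | 7.7% |
| 3 vs 0 | −4.1% | 12.3% |
| 4 vs 0 | −5.5% | 16.3% |
| 3 vs 1 | −2.8% | 9.0% |
| 4 vs 1 | −4.2% | 13.5% |

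(4000 simulated trials per row.)

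Expressed as exit rates:
- 10% vs 5% (20 × 0.10 = 2 vs 20 × 0.05 = 1 infant expected): 6.5 to 7%.
- 30% vs 10% (6 vs 2 expected): 20 to 23% across repeat runs.

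**5. Benign cases.**
- Exits unrelated to evacuation time, even at 30% vs 10%: omitting them leaves a mean difference in medians of about 0.0 days, which is the correct answer for evacuation time.
- Equal exit rates: neither arm is systematically favoured.

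**6. All infants retained with their observed day of last meconium.** Nobody is removed, so the first row of the table applies and the error rate is nominal.

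**The case against.** The strongest reply is that exclusion is inferred. The withdrawal section is a heading and four terms. It does not say that data collection stops or that anyone is left out of the analysis, and the Design section continues charting without exception. That stands, and it is why the point is a contradiction with a conditional consequence. A reader might infer that the protocol drops these infants; its text does not establish this.

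Analysis sets and censoring rules are commonly left to an SAP, which is not shown. That also stands for their detail. But an SAP cannot recover stool data that were not collected because the infant had left the study, and the withdrawal wording is fixed in the protocol.

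For death, a log-rank test that censors deaths still validly compares cause-specific hazards; what fails is reading the Kaplan-Meier curve as a probability of evacuation. So informative censoring mainly concerns the three bowel events.

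Three stronger readings fail:
- That safety is not recorded. Abdominal condition, gastric residuals, feeding intolerance and stooling pattern are charted daily, and the four events would be known as withdrawal reasons. What is missing is a planned comparison by arm.
- That harm of about 2 days would be hidden. With a median of 8 days, log-SD 0.5 and exits of 30% vs 10% unrelated to evacuation time, scoring every exit as never evacuated puts osteopathy 2.2 days behind. That gap comes from changing the outcome definition, at rates no section supports. It also contradicts the Design definition when an infant with NEC or ileus later passes its last meconium.
- That the small sample proves the point. With no events in 20 infants the one-sided 95% upper bound is 1 − 0.05^(1/20) = 13.9%, but this reflects the sample size and is the same whatever the withdrawal rule.

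**Conclusion.** The point holds as a conflict between two sections and as a risk of bias conditional on how it is resolved. If withdrawal ends follow-up, the planned analyses can be biased towards the arm that loses more of its slow infants. In the adverse case, false favouring of osteopathy rises from 2.5% to about 7% at 10% vs 5% exits and to about 20 to 23% at 30% vs 10%. These figures assume 20 per arm, a two-sided test, no true effect, and that the infants who exit are the slowest. The protocol gives no rates, so neither the direction nor the size of any actual bias is known, and with equal rates or exits unrelated to evacuation time there is little or none. Separately, the stated safety aim has no planned comparison by arm.

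**What to change.** - Reword Adverse events and withdrawal so that leaving the study is separate from any decision on study treatment, which stays as the sponsor sets it. Reconcile it with Design by stating that stool charting continues to NICU discharge or transfer after such an event.
- Analyse every randomised infant in the assigned group, using the observed day of last meconium whenever it occurs, including after ileus, volvulus or NEC.
- State that the last stool before an event is not taken as completion.
- Treat death before complete evacuation as a competing event in the time-to-event analysis, or as the worst rank in the Mann-Whitney test.
- Report ileus, volvulus, NEC and death by arm with exact 95% confidence intervals, to serve the safety aim.

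The cost is a few sentences and one analysis rule; the charting is already planned. The small downside is that the primary result may look less favourable.

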**Statistics:**

**Sample size:**

Based on studies investigating meconium passage in VLBW infants [7], a sample size estimation [11] indicated that a total of 40 infants would suffice to detect a 20% difference in the outcome between the groups with a power of 80% and a significance level of 0.05

**Primary outcome:**

time to complete Meconium evacuation in days.

**Secondary outcome:**

introduction of enteral feeding in days, feeding volume on day 14th

time to full enteral feeding in days,

**Statistical analysis** :

Given the non-normal distribution of the data, all comparisons will be performed using non-parametric tests. The Mann-Whitney U test will be used to detect treatment effects between the groups. Kaplan-Meier curves will be plotted to visualize differences in the time to complete meconium evacuation between the groups. Comparison of the curves will be performed using the log rank test. Multiple Cox regression models will be used to identify the possible influence of the covariates birth weight and GA. For all tests, a p-value < 0.05 was considered to indicate statistical significance. SPSS statistical software system (SPSS Inc., Chicago, IL, version 10.0) will be used for all calculations.

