**Design:**

The study design is performed as a prospective randomized controlled trial at the Neonatal Intensive Care Unit (NICU), Department of Pediatrics, Medical University of Vienna/Austria. Infants with a birthweight <1500g and a GA <32 weeks will be included, stratified according to their GA ( < 28 vs. ≥ 28 weeks) and assigned randomly to the intervention or control group. Randomization assignment is performed using sealed opaque envelopes that are grouped in an even blocked size design (block size 4) by stratification variable (GA).The study will be approved to the Ethics Committee of the Medical University of Vienna. Written informed consent will be obtained from the parents after full explanation of the procedure. Infants will be treated according the same standard care procedures for VLBW-infants used at our department.

Study groups:

Infants in intervention group will receive osteopathic treatment within their first 48 hours of life according the following protocol:

All techniques are applied in the supine position:

1. Global listening- any further treatment methods employed to improve mobility must be slow and gentle
2. Release lower ribs and thoracic diaphragm
3. Small intestine diagnosis- Lifting the gut and bringing it to a stillpoint
4. Root of mesentery diagnosis (and manipulation)
5. Mobilisation of the ileocoecalic valve
6. Mobilisation of colon ascendens, transversum, descendens
7. Root of sigmoid diagnosis and manipulation
8. As the 10th cranial nerve influences the intestines’ function by relaxing the sphincters and thus increases gut motility treatment of the parasypmatic nerval system should be always in involved

The treatment algorithm will be repeated three times during the first week of life.

No intervention is planned in the control group.

After admission of the patient to NICU, the infant received primary care according to

the standard principles of neonatal intensive care (monitoring of oxygen saturation,

heart rat, blood pressure, temperature, fluid intake and urine rate, intravenous access

by periphery or central venous line).

The nursing staff assesses the quality of stools as “meconium” (black, thick, sticky) or

“non meconium” by appearance and documented data into the “carevue”

documentation system.

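### Randomisation is stratified by gestational age, but the tests named for the treatment comparison are not; if gestational age is prognostic they become conservative and lose power

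*Protocol*

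**What the plan says.** Under Design, the protocol has infants "stratified according to their GA ( < 28 vs. ≥ 28 weeks) and assigned randomly to the intervention or control group", using sealed envelopes in blocks of four within each GA stratum. The primary outcome is "time to complete Meconium evacuation in days".

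The Statistical analysis paragraph names three methods:

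- **Rank test:** "The Mann-Whitney U test will be used to detect treatment effects between the groups". This test is unstratified by construction.
- **Kaplan-Meier curves:** "Comparison of the curves will be performed using the log rank test". Nothing is said about strata.
- **Cox models:** "Multiple Cox regression models will be used to identify the possible influence of the covariates birth weight and GA". The stated aim is the influence of the covariates. A treatment term is neither named nor excluded.

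Under Sample size, "a total of 40 infants would suffice to detect a 20% difference in the outcome between the groups", with 80% power at the 0.05 level. No standard deviation, control-group value or GA effect is given.

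**The concern.** Blocking within GA strata forces the arms to be nearly balanced on GA, so differences between the strata largely cancel out of the treatment comparison. A pooled rank or log-rank test does not use this. It computes its null variance as if GA could still fall unevenly between the arms, and so counts the difference between strata as noise. If GA affects the outcome, the test statistic is too small on average: the real type I error drops below the nominal 5%, and power drops with it.

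At stake is efficiency in a trial of 40 infants. A null result from a needlessly conservative test would be harder to interpret, although the information that avoids this is already recorded.

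**Working it through.** **The plan's own figure.** The 80% power with 40 infants cannot be reproduced, because no standard deviation is stated. Reading 20% as a relative difference in means, two-sided, with 20 per arm, the coefficient of variation that gives 80% is 0.20 / [(1.96 + 0.84) × √(2/20)] ≈ 0.226. The document neither confirms nor refutes that value, so the check below concerns only pooled against stratified tests.

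**Inputs from the protocol.** 40 infants, two GA strata, blocks of four, outcome in whole days, 5% level.

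**Assumptions.** 20 infants per stratum, log-normal times with within-stratum log-SD 0.5, median 7 days unless noted, times rounded up to days, no censoring. The GA shift is in within-stratum SDs; for example, 0.8 log units / 0.5 = 1.6 SD. A 35% reduction is −ln(0.65)/0.5 = 0.86 SD and a 20% reduction is −ln(0.80)/0.5 = 0.45 SD.

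**Step 1: approximation.** With two equal strata a shift of b SD apart, pooling multiplies the variance by 1 + b²/4. The nominal cut-off of 1.96 then acts like 1.96 × √(1 + b²/4):

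- b = 0.5: 1.96 × √1.0625 = 2.02, type I error about 4.3%
- b = 1.0: 1.96 × √1.25 = 2.19, about 2.8%
- b = 1.6: 1.96 × √1.64 = 2.51, about 1.2%

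**Step 2: simulation of the Mann-Whitney (MW) test against van Elteren (VE, the GA-stratified Wilcoxon test).**

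| GA shift | MW type I error | Power at 35% reduction, MW vs VE | Power at 20% reduction, MW vs VE |
|---|---|---|---|
| 0 | 5% | 73% vs 73% | 26% vs 26% |
| 0.5 SD | 4% | 71% vs 72% | 24% vs 26% |
| 1.0 SD | 2.6% | 66% vs 74% | 19% vs 26% |
| 1.6 SD | 1% | 51% vs 74% | 12% vs 26–27% |

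The type I error and 35% columns use 2,000 trials per cell, so the Monte Carlo error on power is about √(0.7 × 0.3 / 2000) = 1 point. The 20% column uses 2,500 trials per cell, except its first row (3,000 trials, median 8 days). The simulated type I errors agree with Step 1.

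**Step 3: other settings.** The following runs use a true effect of 0.93 SD, median 8 days and 5,000 trials per cell.

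- Log-rank against GA-stratified log-rank, power at shifts of 0, 0.5, 1.0 and 1.5 SD: 77% vs 76%, 75% vs 76%, 68% vs 75%, 59% vs 74%. Pooled log-rank type I error: 5.6%, 4.7%, 3.7%, 2.1%. Stratified: 5.1% to 5.7%.
- Strata of 12 and 28 instead of 20 and 20, Mann-Whitney against van Elteren at the same shifts: 80% vs 79%, 78% vs 79%, 72% vs 79%, 65% vs 79%. The pattern is the same.
- With no GA shift, stratifying costs 1 point or less in these runs.

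**The case against.** The strongest case on the other side has four parts.

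- **The loss is conditional.** The protocol gives no GA effect and does not say why GA was chosen as the stratification factor. A reader might infer that the planned tests are conservative as a matter of fact. The document does not support that: at a shift of 0.5 SD or less the loss is 2 points or less. This stands, which is why the result is given as a range starting at zero.
- **GA is not ignored throughout.** Cox models with GA and birth weight are planned, and their wording does not exclude a treatment term. This stands in part. The gap is narrower than a complete omission of GA: no adjusted or stratified analysis is designated as the treatment test.
- **Stratifying the log-rank test could be an analysis-plan detail.** Silence is not a decision to pool. This is fair for the log-rank test. It does not cover the Mann-Whitney test, which the protocol itself names for detecting treatment effects.
- **The error is in the safe direction.** This stands. The false-positive risk goes down, and the Mann-Whitney comparison is not biased.

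A reader might also infer that the trial has little power to begin with. The protocol states 80% and gives no standard deviation to test that against. The 26% in the table follows from the assumed log-SD of 0.5 and from reading 20% as a reduction in days; it is not a finding about this trial. Sample size is a separate matter.

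**Conclusion.** The mismatch is real: randomisation uses the GA strata and the named treatment tests do not. If GA is prognostic, the pooled tests are conservative and lose power. For a 35% reduction, the Mann-Whitney loss is about 0 points with no GA shift, 1 to 2 at 0.5 SD, 8 at 1 SD and 23 at 1.6 SD. For a 20% reduction, it is about 0, 2, 7 and 14 points.

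The direction follows from the design. The size rests on the assumed GA shift, within-stratum spread, strata sizes and absence of censoring, none of which the protocol fixes. The change is worth making because the trade is lopsided: next to nothing is lost if GA does not matter, and a useful amount is gained if it does.

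**What to change.** In the Statistical analysis paragraph:

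- Replace the Mann-Whitney U test with the van Elteren test, stratified by GA below 28 weeks against 28 weeks or more.
- Specify that the log-rank test is stratified by the same two groups.
- State that the treatment hazard ratio, with its 95% confidence interval, comes from a Cox model that includes treatment and is stratified by GA.

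Which of these tests is primary, and whether birth weight should be added to the Cox model, are separate questions that this point does not settle.

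The cost is wording only. GA is already recorded before the first treatment and used at randomisation, so no new data are needed. If GA turns out to have no effect, the price is at most about 1 to 2 points of power.

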**Studyproposal**

**Titel:**

**The impact of visceral osteopathic treatment on the meconium evacuation in very low birth weight infants**

**Masterthesis Osteopathy by Doz. [name]**

**at the Donauuniversity Krems**

**Introduction:**

The physiologic immaturity of the intestinal motor mechanisms and the associated feeding problems are one of the challenges for neonatologists in the treatment of very low birth weight infants (VLBW- infants= with a birthweight <1500gram). Timing of the first and last meconium stool is critical for oral feeding tolerance and proper gastrointestinal function [1]. The vast majority of term infants (99.8%) pass their first meconium within 48 hours of life [2], while premature infants show a wide variability. The time to pass their first meconium ranges from 1 hour to 27 days (median: 43 hours) ([3, 4]. Obstruction of the gastrointestinal tract by tenacious, sticky meconium frequently leads to gastric residuals, a distended abdomen and delayed food passage. Recent data support the concept that complete rapid evacuation of meconium plays a key role in feeding tolerance [5]. Duration to full enteral feedings is extended, the probability to acquire infections due to intravenous access for parenteral nutrition increases and hospital stay of the infant prolongates. Data from a study including 21 preterm infants with the diagnosis “Meconium obstruction in the very low birth weight premature infant” showed that tenacious meconium is most frequently located in the distal ileum [6]. In that study, various kinds of enemas were demonstrated to be effective and safe for promoting the evacuation of tenacious meconium plugs during or shortly after instillation. Resolution of obstruction with glycerin suppositories, saline, acetylcystein or non-absorbable contrast media was conducted in 70% of symptomatic infants, thereby avoiding surgical removal of the plug. Recently, the study group around Haiden et al performed a prospective randomized trial; to determine whether repeated prophylactic applications of small volume glycerin enemas are effective in accelerating passage of meconium in VLBW infants [7]. The authors did not find a correlation between application of enemas and meconium evacuation. A reason for the ineffectiveness of glycerin enemas was supposed to be that the volume used was too small to mobilize tenacious meconium sufficiently from deep parts of the colon and small bowel (Colon ascendes, terminal Ileum).

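### Pre-treatment stooling is recorded but used in no stated analysis; a yes/no item fixed at randomisation should be a prespecified covariate in a model that estimates the treatment effect

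*Protocol*

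**What the plan says.** - **Baseline data.** The pre-treatment list under Data collection includes "Stooling pattern". In the Design section, nurses classify stools as meconium or not, so whether any meconium has been passed can be derived.
- **Endpoint.** "The time to complete meconium evacuation is defined as day of life on which the last meconium was passed".
- **Randomisation.** Infants are "stratified according to their GA ( < 28 vs. ≥ 28 weeks" and envelopes are "grouped in an even blocked size design (block size 4) by stratification variable (GA"). Stool status plays no part.
- **Background.** For premature infants the Introduction says: "The time to pass their first meconium ranges from 1 hour to 27 days (median: 43 hours"). The first treatment falls within 48 hours of birth.
- **Analysis.** The Statistical analysis paragraph gives the detection of treatment effects to the Mann-Whitney U test and the comparison of the Kaplan-Meier curves to the log rank test, neither with covariates. On regression it says: "Multiple Cox regression models will be used to identify the possible influence of the covariates birth weight and GA". It does not say that the Cox model contains treatment group.

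**The concern.** First and last meconium mark the start and end of the process that the trial measures. Infants who have already started at entry may well finish earlier. By the Introduction's own figures, entry status divides the sample: some infants will have started and many will not. Of the recorded baseline items it is the closest to the endpoint, yet neither the randomisation nor any stated analysis uses it.

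In a trial of about 40 infants the arms can differ noticeably on such an item by chance, even within a GA stratum. At stake are the precision of the treatment estimate and how far a result can be trusted in a trial that happens to be unbalanced.

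**Working it through.** **The plan's own figure.** The Sample size section reads: "a total of 40 infants would suffice to detect a 20% difference in the outcome between the groups with a power of 80" per cent; alpha is 0.05. It gives no SD, control value or scale for the 20%, so 40 cannot be reproduced from what is stated. Reading it as a 20% difference in means, two-sided, 20 per arm, the coefficient of variation (CV) would have to be 0.20 / ((1.960 + 0.842) × √(2/20)) = 0.226. That back-solved value is used only as a reference point.

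**Inputs.** 20 v 20 is assumed, because the ratio is not stated. The share p of infants who have passed meconium by randomisation is not given. It is near 50% only if randomisation comes late in the 48-hour window (median 43 hours), and lower if earlier. If age at randomisation were uniform over 0 to 48 hours and first-meconium time lognormal (median 43 hours, log-SD 0.8 to 1.2, both assumed), p would be 24% to 29%. The range used is 10% to 50%. The correlation ρ between log first- and log last-meconium time is not in the protocol; 0.3, 0.5 and 0.7 are assumptions.

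**Step 1: chance imbalance.** With X₁ and X₂ independent Binomial(20, p), a gap of 20 points is 4 infants of 20:

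| p | P(gap ≥ 4 of 20) |
|---|---|
| 0.10 | 6.3% |
| 0.30 | 22.6% |
| 0.50 | 26.8% |

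In a simulation with GA-stratified blocks of 4, and GA correlated 0.3 to 0.5 (assumed) with first and last meconium, such a gap still occurred in about 20% of trials. Stratifying by GA does not remove it.

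**Step 2: what the yes/no item could explain.** R² = ρ² φ(z_p)² / (p(1 − p)), where φ is the normal density and z_p the p-quantile. Equivalent information from 40 infants is 40 / (1 − R²).

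- p = 0.50: φ(0)² / 0.25 = 0.637, so R² = 0.637 × (0.09, 0.25, 0.49) = 0.057, 0.159, 0.312, or about 42, 48 and 58 infants.
- p = 0.10: φ(1.28)² / 0.09 = 0.342, so R² = 0.031, 0.086, 0.168, or about 41, 44 and 48 infants.

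These are upper figures, because GA may already carry part of the information.

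**Step 3: power beyond GA.** With GA already in the model, simulated power changed by about −2 to +1 points at ρ up to 0.3, +2 to +4 at 0.5, and +7 to +10 at 0.7.

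**Step 4: validity of the unadjusted test.** At the null, simulating a yes/no item at 50% prevalence without GA, the Mann-Whitney test rejected in 4.6% to 4.9% of trials for item-endpoint correlations r from 0 to 0.7. Among trials with a gap of at least 5 infants it rejected in about 7%, 12% and 17% at r = 0.3, 0.5 and 0.7, against 4% to 5% with adjustment. Here r is the correlation of the yes/no item itself, so r = 0.5 is a stronger link than ρ = 0.5 (which gives r = √0.159 = 0.40). With GA adjusted, the rates in unbalanced trials were about 5%, 6% to 9%, and 10% at ρ = 0.3, 0.5 and 0.7 without the item, and 4% to 6% with it.

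**The case against.** The strongest reply is that nothing here is an error. Naming two covariates contradicts nothing, a third could be added in a SAP that is not shown, and every baseline item can be unbalanced by chance. This stands in part: the point is an improvement, not the correction of a misstatement. But the protocol does not leave covariates open. It names two and omits the recorded item nearest the endpoint.

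A second reply is that randomisation keeps the unadjusted test valid. That stands in full. A reader might infer that the omission biases the comparison or inflates the type I error, but the overall error rate is at its nominal level whatever the correlation. Only precision, and error conditional on an unbalanced allocation, are affected.

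A third reply is that the gain is unproven, since the covariate reflects first meconium and the endpoint is the last. That also stands. A reader might infer from the 43-hour median that half the infants will have started, and that power is certainly being given up. Neither follows: the median bears on the end of the treatment window and not on randomisation, whose age the protocol does not give, and the correlation is unknown. Nor would adjustment rescue a badly underpowered design: with a CV of 0.6 and a 20% difference, power would move only from 18% to 23% at r = 0.5.

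Finally, a term added to a Cox model meant only to examine covariates would leave the treatment comparison as unadjusted as before. This is correct, and it determines how the fix must be worded.

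**Conclusion.** The point holds as a modest, nearly free improvement. Pre-treatment stooling is collected, plausibly prognostic and unused, and the stated treatment comparisons adjust for nothing. A chance gap of 20 points or more would occur in about 6% to 27% of trials, for prevalence from 10% to 50% and 20 infants per arm. Beyond GA, the power gain runs from about nil to roughly 10 points, depending on a correlation that the protocol does not supply.

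The recorded item also needs a common time point. It is tied to the first treatment, an event that control infants do not have, so as listed it is not a like-for-like baseline in the two arms.

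**What to change.** In the Statistical analysis paragraph, state that the Cox model for time to complete meconium evacuation includes treatment group and gives the adjusted treatment effect. Name GA, birth weight and any meconium passed before randomisation (yes/no) as its prespecified covariates.

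Under Data collection, define that item in both arms from the nursing stool record at the time of randomisation and not at the first treatment. Settle this before outcome data are seen; added later, it would be post hoc.

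The cost is one tick box at randomisation, since the stool record already exists, and one more term in a model with about 40 events at most. If the correlation proves low there may be no gain in power, or a very small loss.
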